### Study design

All procedures involved in this trial will be conducted in compliance with the National Statement on Ethical Conduct in Human Research and the Australian Code for the Responsible Conduct of Research. The study was approved by the Monash University Human Research Ethics Committee, Melbourne Australia (Project ID: 35502). The study was designed according to the Strengthening The Reporting of Observational studies in Epidemiology (STROBE) statement [23]. STROBE check list is provided as an additional file.

The ENJOY IMP-ACT study is an implementation research project employing a hybrid II implementation-effectiveness pre-post mixed method design [24]. We will implement and evaluate the implementation intervention, process and impact using the Reach, Effectiveness, Adoption, Implementation, and Maintenance (RE-AIM) Framework [25] and our adopted logic model (see Fig. 1). Six sites in Victoria, including two regional sites, will participate in the study with a pragmatic staggered commencement. Each site will have a 3-month control period followed by 9-months implementation intervention (TERM framework intervention: Training, Engagement, Resources development, Marketing and promotion), and a maintenance phase (3 months) (Fig. 2). The pre-post design is a pragmatic real-world design where all local governments will receive the implementation intervention framework. A control period will act as the waiting list ‘control arm’.

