##### Intercept surveys

Each site will have a 3-month control period followed by a 9-month implementation intervention period (TERM—Training, Engagement, Resources development, Marketing and promotion), and a maintenance phase (3 months). Evaluation (observation of users/visitors and onsite intercept surveys) will take place each month during the control period (baseline = B), every 3 months during implementation intervention phase (I1, I2, I3), and once during the maintenance phase (M1), see Table 2 and Fig. 2. The control period will include three evaluation points (B1, B2, B3), each occurring over a 10-day period per month (including one weekend). The time series evaluation will enable controlling for variations in equipment access due to weather (seasonal effects). Potential participants (park users in the specified target area) will be approached by trained, clearly identifiable research staff to see if they meet inclusion criteria. They will be provided with a verbal explanation about the study and all ethical considerations and invited to participate in a survey. Interested participants will then be asked to provide a verbal agreement (consent) to participate. Upon verbal consent, a paper survey will be administered by the researcher onsite. If more than one person is in the park during any observation period, the research staff decision of who to approach would be guided by aiming to overall recruit an equal number of men and women. The participants will be eligible to complete only one intercept survey during the baseline and maintenance period. During the intervention period the same participants can be surveyed multiple times.

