### Statistical methods

#### Sample size estimation and justification

##### A target outcome for successful Seniors Exercise Park usage

A NSW study demonstrated only 5.3% (*n* = 6) of older adults (> 60 years) utilise outdoor exercise equipment at a park [36]. In our field work we observed 10 older adults independently using the Seniors Exercise Park in a typical week following installation without any promotion or supported implementation. We anticipate that following the implementation intervention, there will be a 100% increase in the number of independent users (*n* = 20) as well as an increase in the number of older adults using the equipment as part of organised classes (*n* = 30) in a typical week (while accounting for weather impact [45]). Therefore, we would expect there will be approximately 50 equipment users observed over a 10-day period per site. This exceeds the reported fourfold usage increase following park refurbishment reported elsewhere [46]. Power calculations using a Poisson or negative binomial distribution, adjusting for site and weather differences [47] demonstrated that a power of over 0.95 can be achieved to detect a 100% increase in park visitors with this sample size.

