##### Sample size calculation for the intercept surveys

Sample size calculations for the intercept surveys as part of aim 2 are based on the expected number of older people who will complete the survey using data from our previous project [22]. We observed 10 older people using the Seniors Exercise Park in a typical week (prior to formal promotion of the newly installed park). We hypothesised that the implementation intervention (TERM) will result in *at least* a twofold increase in the number of older people using equipment at the completion of the intervention phase (I3) compared to baseline (B1,B2,B3), with a 20% attrition rate (proportion of people refusing to be interviewed) during the maintenance phase (M1). Assuming 25% will decline to participate or have previously completed the survey [40], we will aim for a total of 54 intercept surveys (8 at baseline; 34 across I1-I3 and 12 at M1) per site, with an overall sample of 324 interviewees across the six sites. Each data collection period will include an observation period of 10 days (instead of a typical 7-day period as commonly used [35]). Increasing the number of observations days to 10 days will enhance opportunities for the research team to recruit more older visitors to complete the intercept surveys to meet the targeted sample size.

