#### Statistical analysis

##### AIM 1—‘TERM’ implementation evaluation and impact

Descriptive statistics will be used to report the overall number of older people using exercise equipment as well as the type of usage and uptake, mobile app access, and survey responses from allied health professionals and seniors leaders. The proportion of missing data will also be reported descriptively, and if more than 10% of data are missing, data will be imputed using multiple imputation techniques. Generalised linear models [47] (with main effects for intervention, site, season and their interaction) will be used to examine the impact of the implementation intervention on the total number of older people (primary outcome) using the equipment with overdispersion handled using a negative binomial distribution. Sensitivity analyses will be undertaken by comparing models with missing data and imputed data.

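### The Aim 1 model has no time term, so its intervention coefficient is a site- and season-adjusted before-after contrast that credits any non-seasonal drift in park use to TERM

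*Protocol article*

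**What the plan says.** The Aim 1 paragraph of the statistical analysis section names the terms of the model for the number of older users: "Generalised linear models [47] (with main effects for intervention, site, season and their interaction) will be used to examine the impact of the implementation intervention", "with overdispersion handled using a negative binomial distribution". It lists no trend, calendar-time or study-month term. The Aim 2 model, by contrast, includes a time-point factor.

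Under Study design, every site is treated: "The pre-post design is a pragmatic real-world design where all local governments will receive the implementation intervention framework". The comparator is each site's own first three months: "A control period will act as the waiting list", followed by the words 'control arm' in inverted commas. Observation is monthly in the control period (B1-B3), three-monthly under TERM (I1-I3) and once in maintenance (M1).

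The one time-related influence that the protocol says it will control is weather and season. The Intercept surveys section states: "The time series evaluation will enable controlling for variations in equipment access due to weather (seasonal effects".

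**The concern.** Aim 1 asks whether the implementation framework raises use. The model as listed tests whether use differs between the earlier and later phases once site and season are allowed for. The two questions coincide only if use would otherwise have stayed level over the year or so of follow-up. If it would have risen anyway, for example by word of mouth or changes nearby, the rise is counted as TERM. A fall would mask a real effect in the same way.

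The staggered starts may put some sites in their control period while others receive TERM, but no term in the Aim 1 model uses calendar time to draw on that overlap. This coefficient bears on a primary outcome and on the case for scale-up.

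**Working it through.** **Inputs from the protocol.** Six sites; windows B1-B3, I1-I3 and M1; 10 older users in a typical week, or 10 × 10/7 = 14.3 per 10 days; target rate ratio 2; negative binomial model.

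**Assumptions, because the protocol gives no figures.** Windows at months 1, 2, 3, 6, 9, 12 and 15; starts 1 to 3 months apart; dispersion k from 0 to 0.25 (to 1 for the power check); growth of 0-10% a month.

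**1. The protocol's power figure.** It states power above 0.95 for a 100% increase. A Wald test on the log rate ratio has variance 1/(n0·μ0) + 1/(n1·μ1) + k(1/n0 + 1/n1). Take n0 = n1 = 18 (6 sites × 3 windows), μ0 = 14.3, μ1 = 28.6 and k = 0.25. The variance is 0.0039 + 0.0019 + 0.0278 = 0.0336, with SE 0.183. Then z = 0.693/0.183 - 1.96 = 1.82, and power is 0.966. Power is 1.00 for k = 0, 0.80 for k = 0.5 and 0.53 for k = 1. The claim reproduces for k up to about 0.25, in a model without a trend.

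**2. How closely phase follows time within a site.** For months 1, 2, 3, 6, 9 and 12, r² between phase and month is 110.25/(1.5 × 93.5) = 0.79, a variance inflation of 4.7. Adding month 15 gives 0.725 and 3.6.

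**3. Spurious ratio from growth alone.** B1-B3 average month 2 and I1-I3 average month 9, so the ratio is about (1 + g)^7: 1.15 at 2% a month, 1.41 at 5%, 1.50 at 6% and 1.95 at 10%. A doubling with no TERM effect needs 2^(1/7) - 1 = 10.4% a month.

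**4. Simulated rejection with no TERM effect.** Site and season main effects were fitted, without the interaction. The third column compares B1-B3 with I1-I3 and counts significant increases only (nominal 2.5%), with k from 0 to 0.25. The fourth uses all seven windows and a two-sided 5% test, with k of 0.10 or 0.25.

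| Growth per month | (1 + g)^7 | Significant increase | Two-sided rejection |
|---|---|---|---|
| 0% | 1.00 | 1.5-4.0% | 4-6% |
| 2% | 1.15 | about 8-38% | 16-29% |
| 5% | 1.41 | not run | 67-94% |
| 6% | 1.50 | about 54-100% | not run |
| 10% | 1.95 | not run | about 100% |

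The fitted ratio at 6% was 1.50-1.58 with six windows. With M1 counted as intervention, the fitted ratio at 2% was 1.19-1.22. Adding a linear month term on the log scale brings rejection back to about 1-4% (nominal 2.5%) and 4-7% (two-sided).

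**5. What the month term costs.** For a sudden doubling with no trend, power with the term is 0.995-1.00 at k = 0, and 0.34-0.84 at k of 0.10 to 0.25 depending on stagger. For a doubling that builds up log-linearly to I3, the stated model detects the increase in 87-100% of trials and the trend-adjusted model in 3-13%. In a run of that kind the adjusted ratio was 1.05-1.11 in place of the true rise.

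**6. What the B1-B3 slope can show.** Ignoring season, the variance of a common monthly slope is (1/14.3 + k)/(6 × 2). At k = 0 this is 0.070/12 = 0.0058, SE 0.076, so the 95% half-width is 0.15 per month on the log scale. At k = 0.25 it is 0.320/12 = 0.0267, SE 0.163, half-width 0.32. Growth of 2% or 6% a month (0.02 or 0.06 on that scale) lies well inside both.

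**The case against.** The protocol calls its design pre-post and pragmatic, follows an observational reporting standard, puts 'control arm' in inverted commas and never claims a concurrent comparator. That stands: the lack of an untreated arm is disclosed and is not the point here.

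A reader might infer that these six parks are newly opened and that use will therefore grow unaided. The documents do not support this. The phrase "prior to formal promotion of the newly installed park" describes the park in the earlier project that supplied the baseline rate. The six study parks are described only as installed and open. Nor does the fourfold rise ("This exceeds the reported fourfold usage increase following park refurbishment reported elsewhere") show background growth. It followed a refurbishment, whereas here installation precedes baseline. The 10 users a week is one level and gives no slope.

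The growth rates are therefore assumed, and the simulations omit the interaction that the protocol lists. Both limits stand. They affect the size of the problem but not its direction.

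The strongest objection concerns the remedy. TERM is delivered over nine months, and the intercept-survey sample size places the doubling at I3, so a gradual effect is plausible. A rule crediting TERM only when the trend-adjusted estimate agrees would then miss a real doubling about nine times in ten. This is accepted, and no such rule is proposed.

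**Conclusion.** The concern holds in a limited form. The Aim 1 coefficient measures a site- and season-adjusted change from before to after, and it equals a TERM effect only if there is no other trend. The terms are written out in the protocol, so this is a stated choice and not a detail left to an analysis plan.

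The size is conditional on growth, dispersion and stagger, none of which the protocol gives. With level use the test keeps its nominal error rate. At 2% growth a month the spurious ratio is about 1.15 and a false significant increase appears in about 8-38% of trials; at 6% the figures are about 1.5-1.6 and 54-100%. It would go too far to say that ordinary growth will be declared a TERM effect, because nothing in the documents shows that such growth is present. This is an inexpensive improvement to what the trial can conclude and does not invalidate its main analysis.

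**What to change.** - Keep the stated model as the main analysis of Aim 1.
- Pre-specify a companion model on all seven windows that adds one log-linear month term to intervention, site and season. With site effects fitted, study month and calendar month give the same adjusted estimate, because they differ only by each site's start date.
- Report the intervention rate ratio with and without the term, and the B1-B3 slope with its interval. A flat-looking slope should not be read as proof of no drift.
- Describe the main estimate as an adjusted before-after change whose attribution to TERM assumes no background trend.
- Reword Study design so that the control period is a within-site pre-period and not a 'control arm'.
- Do not make the trend-adjusted test a condition for attribution.

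The cost is some wording and one further model on data already planned. The downside should be stated with it. The companion's power for a sudden doubling runs from roughly 0.4 (0.34 in the least favourable setting run) to 1.0, so the stated power above 0.95 does not carry over. The companion also absorbs almost all of an effect that builds up gradually. A null companion result is therefore not evidence against TERM.

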##### AIM 2—evaluation of the ENJOY Seniors Exercise Park on physical activity and wellbeing

Summary statistics will be used to describe the demographic, socioeconomic, equipment usage and health-related characteristics of Seniors Exercise Park area users at each time point. Data will also be examined and reported relative to the adult general public, based on the distribution of age, marital status, and country of birth (using Australian Bureau of Statistics census data for each local government area). Linear and logistic regression models (with main effects for site, time-point, season and their interaction) will be used to examine the impact of the implementation intervention on physical activity level (primary outcome) and other health user characteristics. Statistical significance of the interaction term will be used to determine if the outcome varied between sites at each intervention time point (I1-I3) or M1 relative to their baseline difference.

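### The Aim 1 count model, read as the full intervention by site by season interaction, cannot be estimated from 42 site-waves; season needs to enter additively, identified by the staggered starts

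*Protocol article*

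**What the plan says.** The Aim 1 analysis section gives the terms of the primary model: "Generalised linear models [47] (with main effects for intervention, site, season and their interaction) will be used to examine the impact", "with overdispersion handled using a negative binomial distribution". The Aim 2 section uses the same construction for physical activity level, the other primary outcome: "Linear and logistic regression models (with main effects for site, time-point, season and their interaction) will be used to examine the impact". It adds that the interaction will show whether sites differ at I1-I3 or M1 relative to baseline.

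The data come from this design (Study design; Intercept surveys):
- "Six sites in Victoria, including two regional sites, will participate in the study with a pragmatic staggered commencement". The order of sites is listed, but no dates or gaps are given.
- "Each site will have a 3-month control period followed by 9-months implementation intervention", then three months of maintenance.
- "The control period will include three evaluation points (B1, B2, B3), each occurring over a 10-day period per month".
- After baseline, evaluation is "every 3 months during implementation intervention phase (I1, I2, I3), and once during the maintenance phase (M1"). The footnote to Table 3 puts M1 at completion of the maintenance phase, which is about month 15.

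On season, the Intercept surveys section says: "The time series evaluation will enable controlling for variations in equipment access due to weather (seasonal effects").

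**The concern.** The article names three factors and then their interaction, in the singular, without saying which. The plain reading is the full crossing of intervention, site and season. Each site is followed for about 15 months in seven waves, so many combinations of site, phase and season are never observed. More scans within a wave cannot fill those empty cells.

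If the stated model cannot be fitted, terms have to be removed, by the software or by the analyst, after the data are seen. The coefficient labelled intervention then depends on which terms survive and how they are coded. Under reference coding it describes one site in one season rather than the trial as a whole. Use of outdoor equipment depends on weather by the article's own account, so the handling of season bears directly on the primary result and should be settled beforehand.

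**Working it through.** **The plan's own figure.** The only stated figure nearby is power above 0.95 for a doubling of users. With a baseline of 10 users, 20 after intervention, six site-waves on each side, Poisson counts and two-sided alpha 0.05 (assumed): standard error = √(1/(6×10) + 1/(6×20)) = √0.025 = 0.158; z = ln 2 / 0.158 = 4.38; power = Φ(4.38 − 1.96) = 0.992. The figure is reproduced, and the point does not turn on it.

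**Inputs.** 6 sites × 7 waves = 42 site-waves. Assumed, because not stated:
- waves at months 1, 2, 3, 6, 9, 12, 15, or at 1, 2, 3, 5, 8, 11, 14;
- gaps between site starts of 1, 2 or 3 months;
- B1 in the first, second or third month of a season;
- four three-month seasons, each wave lying in one of them.

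This gives 2 × 3 × 3 = 18 schedules. Intervention is coded as control/post (binary) or as control/implementation/maintenance (three phases).

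**Aim 1: parameters against rank of the design matrix.**

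| Model | Parameters, binary | Rank | Parameters, three phases | Rank |
|---|---|---|---|---|
| Full three-way | 6×4×2 = 48 | 30–36 | 6×4×3 = 72 | 30–36 |
| All two-way | 1+5+3+1+5+3+15 = 33 | 30–33 | 1+5+3+2+10+6+15 = 42 | 30–36 |
| Phase × site, season additive | 10+5 = 15 | 15 | 11+10 = 21 | 21 |
| Main effects only | 1+5+3+1 = 10 | 10 | 1+5+3+2 = 11 | 11 |

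The binary all-two-way model reached 33 of 33 in 12 of the 18 schedules, with 42 − 33 = 9 residual degrees of freedom. It was deficient in the other 6. Both models with additive season were full rank in all 18.

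**Aim 2.** Site by seven time-points has 6 × 7 = 42 parameters and rank 42. Adding season leaves the rank at 42 in all 18 schedules, because each site-by-time-point cell lies in one season. The full three-way form has 6 × 7 × 4 = 168 parameters and rank 42. With B1–B3 pooled into one level, site by five time-points has rank 30, and adding three season terms gives 33 of 33 in 12 schedules, 32 in 4 and 30 in 2. Without the site by time-point term, the additive model has 1 + 5 + 4 + 3 = 13 parameters and is full rank in all 18.

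**Where seasonal information comes from.** M1 at month 15 is the calendar month of B3 a year later (month 14 matches B2), so M1 shared a baseline season at every site in every schedule. At most one of I1–I3 did so at any site, which makes 0 to 6 of the 18 implementation site-waves. If B1 opens a season and waves fall at months 6, 9 and 12, none does: within that site the comparison of baseline with I1–I3 is confounded with season, and only the other sites' different calendar positions separate the two.

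**Price of additive season.** Under the staggered schedules, season adjustment inflates the variance of the intervention effect by a factor of 1.0 to 1.5. With waves at months 6, 9, 12 and 15, power for a doubling is about 1.0 for Poisson counts, 0.987 to 1.0 at dispersion 0.1, 0.86 to 0.97 at 0.25 and 0.63 to 0.83 at 0.5. No dispersion value is stated, so these values are assumptions.

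**The case against.** The best defence is that an estimable reading exists. The Aim 2 section describes its interaction as a comparison of sites across time-points. Carried to Aim 1, this gives intervention by site with additive season, which is full rank (15 of 15, or 21 of 21). That stands, and it shows that the design can support a sound analysis. It does not rescue the text, which lists season among the interacting factors and does not select this reading. In Aim 2 itself, the same reading with seven separate time-points leaves season with nothing to contribute.

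A second defence is that the article condenses a fuller plan, and exact terms are often left to that plan. This would answer silence. Here the article does state the terms of the primary model, and on their plain reading they cannot be fitted.

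Third, every rank depends on assumed dates. This is true, and it matters for the two-way binary model and for pooled Aim 2, where results vary by schedule. The failure of the three-way model appeared in every schedule tried.

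A reader might go further and infer that each phase falls in its own season within a site, or that seasonal control does not exist. The documents support neither. M1 returns to a baseline season, implementation alone spans several seasons, a control block that straddles a season change can share a season with one implementation wave, and the planned stagger identifies an additive season effect. Nor does the seasonal sentence in the Intercept surveys section say that control works within a single site; it only leaves the source unstated.

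**Conclusion.** The concern holds in a limited form. The Aim 1 model as worded is not estimable as a three-way interaction (rank 30–36 of 48 or 72). With all two-way terms it is always deficient with three phases, and deficient or close to saturated with a binary term. In Aim 2, season is redundant beside site by seven time-points, and estimable in most but not all schedules if B1–B3 are pooled. The design itself is adequate for an additive season adjustment. That adjustment rests on the staggered starts, on a seasonal pattern common to all sites, and on M1 matching the baseline season; it does not rest on each site's own series. These results assume the start gaps, wave months and four-season coding listed above. The stagger is necessary: if all six sites started together at the opening of a season, with implementation coded apart from maintenance, even the main-effects model would lose rank (10 of 11).

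**What to change.** - **Aim 1:** state the primary model as negative binomial with phase, site and season, season additive only. Report the site-averaged phase effect. Fit site by phase as a separate heterogeneity analysis. Drop all season interactions.
- **Aim 2:** pool B1–B3 as one baseline level and keep season additive. Estimate the main effect from the model without site by time-point, and use that interaction only for the heterogeneity test.
- **Sensitivity check:** report M1 against B1–B3 as a season-matched comparison. It concerns maintenance, so it should not replace the hypothesis of I3 against baseline given in the intercept-survey sample size section.
- **Intercept surveys section:** reword the seasonal sentence to say that season is controlled through the staggered starts across sites.

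The cost is analysis wording only, with no new data. The downside is the assumption that all six sites, metropolitan and regional, share one seasonal pattern; this should be stated as a limitation.
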